## Specimen collection and laboratory studies

The following samples will be collected for HIV and RTI testing when indicated in the protocol (see Table 2):

1. Blood (venipucture) for HIV and CD4 count will be conducted once at the beginning of the study.
2. HIV plasma viral load will be conducted at each baseline, a total of three times
3. Cervical/endocervical swab will be used to collect a pap smear specimen once at the second screening visit
4. Cervical swab for HPV testing at screening visit #2 and at each of the day 14 visits, a total of 4 swabs
5. Swabs (2) of the posterior fornix and endocervix for diagnosis of sexually transmitted infections will be collected at the second screening visit and day 28 of the 3rd arm, and repeated if signs or symptoms of STI develop during the study period (Total swabs’ 4).
6. Swabs (2) of the posterior fornix for Gram stain and pH, will be collected at each study visit in which an exam is conducted (Total swabs’22 )
7. Syphilis serologic testing will be conducted once at the beginning of the study unless a genital ulcer or other suggestive symptoms are identified
8. CVL specimens will be collected during each study visit in which a clinical exam is conducted, to measure cervico-vaginal HIV viral load by introducing 5 ml of PBS into the vagina and collecting the pooled fluid in the posterior vaginal fornix. A total of 16 CVLs will be obtained from each woman during the study.
9. Two vaginal swabs will be used during each pelvic exam during the study to collect cervico-vaginal HIV viral load samples (20 swabs). At the second exam (“acute effects” assessment) on day 0 of each arm, four swabs will be used to collect the cervico-vaginal HIV viral load samples (12 swabs)(Total swabs’ 32).

9) Urine pregnancy test at screening #2 and each baseline visit (4 urine samples)

10) Genital ulcer sample collection (if genital ulcer present clinically)

11) A swab will be collected at each study visit to test for semen contamination (11 swabs)

12) HSV-1 and HSV-2 serology on stored blood specimens from all baseline clinic visits (Total of 3 visits per woman - 180 stored specimens total).

13) Cytokine testing on stored CVL specimens from all baseline clinic visits and all day 7 visits (Total of 6 visits per woman - 360 stored specimens total).

All laboratory specimens from each visit will be identified by the same specimen number using pre-printed waterproof stickers. The specimen number will be recorded in the corresponding visit case record form and in a specimen logbook.

The majority of testing will be done at the TUC laboratory in Bangkok. Selected specialized HIV and STI testing will be conducted at CDC in Atlanta, and trichomoniasis testing and limited testing for candida will be conducted at Chiang Rai Health Center.

For each of the indications below, the following tests will be conducted:

*Trichomoniasis vaginalis*: The InPouch culture test (BioMed Diagnostics, San Jose, California, USA) from a swab of the posterior fornix to detect *T. vaginalis.* With the InPouch system more than 90% of positive cultures are identified within the first 24 hours. *In vitro* testing has shown that Carraguard could interfere with trichomonas growth at 48 but not at 24 hours (17).

*Candida sp*: Gram stain will be used to detect *Candida sp.*

*Bacterial vaginalis:* Gram stain will be used to assess the vaginal flora for BV, using the Nugent criteria. For women with symptoms, Amsel criteria will also be used.

*N. gonorrhoeae and C. trachomatis*: A COBAS Amplicor polymerase chain reaction (PCR) (Amplicor, Branchburg, NJ, USA) *N. gonorrhoeae* and *C. trachomatis* test will be conducted from an endocervical specimen. A modified collection and processing procedure using a chlamydia transport medium and a PBS wash will be used to eliminate all inhibition from the Amplicor test (17).

Syphilis: A non-treponemal, rapid plasma reagin (RPR) test (MacroVue RPR Card Test, Becton Dickinson Microbiology Systems, Cockeysville, Maryland, USA) will be used for the serological detection of syphilis infection. A reactive syphilis test will be confirmed by the *Treponema pallidum* particle-agglutination assay (TPPA; TPPA Reagents, Fujirebio Inc., Tokyo).

Etiology of genital ulcer disease will be determined by a genital ulcer, multiplex polymerase chain reaction (PCR) assay ([name]'s lab, CDC) for the presence of *H. ducreyi*, *T. pallidum*, and Herpes simplex virus (HSV).

Human papillomavirus (HPV): Cervical swabs will be tested for HPV using L1 consensus PCR with the PGMY09/PG MY11 primer set. The resulting PCR products will be typed using a line blot assay (developed by Roche Molecular Systems, Alameda, CA).

Cervical cytology: Cytology will be performed by pathologists at Chiang Rai Hospital laboratory.

HIV: an enzyme immunoassay (EIA, Genetic Systems HIV-1/HIV-2 EIA, Genetic Systems Corp., Redmond, Washington) will be used for screening. A Western blot (WB, NovaPath HIV-1 Immunoblot, BioRad Diagnostics Group, Hercules, California) will be used for confirmation.

CD4 count: Lymphocyte phenotyping will be performed on venous samples collected in EDTA collection tubes using the FACScan flow cytometer (Becton Dickinson Immunocytometry Systems, San Jose, CA, USA) and the standard six-tube, two-color monoclonal antibody panel (Becton Dickinson).

HIV plasma viral load: HIV RNA levels in the plasma will be determined by using the Amplicor HIV-1 Monitor Test, version 1.5 (Roche Diagnostic Systems, Branchburg, NJ), a quantitative reverse-transcriptase PCR assay. The lower quantification limit for the standard Monitor assay is 400 copies/ml, and the lower quantification limit for the Ultrasensitive Monitor assay is 50 copies/mL.

Cervico-vaginal HIV viral load measurements: Five milliliter (PBS) CVL samples will be examined for blood by visual inspection and with the use of a Multistix-8 SG Urine Strip (Bayer Inc., Elkhart, IN) that measures whole blood and hemoglobin. If blood is present by Multistix-8, hemoglobin concentrations will be used to calculate blood volumes in CVL.

The cervico-vaginal samples will be separated into cellular and cell-free fractions by low speed centrifugation (400 x g). A 1.0 ml aliquot of CVL supernatant will be used to calculate the HIV-1 RNA copies per total CVL. Cell-free, virion-associated HIV-1 RNA in CVL will be quantified using the Roche Amplicor Monitor HIV-1 ver.1.5 kit (Roche Diagnostic Systems, Branchburg, NJ), per the manufacturer’s protocol, with the exception that viral pellets will be obtained by centrifugation (1 x 105 x g) for 60 minutes and a NucliSense wash will be used to extract the viral RNA prior to running the amplicor test. The CVL cell pellets will be used to test for cellular replication of HIV-1 in vaginal secretions using a semiquantitative test for spliced HIV-1 mRNA. Infectious virus in CVL will be measured using a recently developed modification of the TZM-bl assay that detects low levels of infectious HIV-1 in female genital secretions.

It is known that Carraguard inhibits the RNA Amplicor test used for the cervico-vaginal supernatant specimens collected during the acute effects assessment if Carraguard is present in high enough quantities. The lab protocol includes a dilution step that may be sufficient; however, if the concentration of Carraguard is too high for RNA testing to be valid, we will replace the RNA Amplicor test with an HIV p24 antigen test of specimens.

**Semen Detection:** Testing to be done on a vaginal swab specimen collected according to manufacture’s instructions (Abacus Diagnostics). If contaminated with semen, the woman will be rescheduled for another CVL and swab collection for within 24-48 hours.

HSV 1 and HSV 2 serology: testing will be done according to manufacturers instructions on stored serology specimens.

Cytokine testing: Cytokine testing will include IL-1 beta and TNF alpha (and may include a broader range of specific cytokines, if resources permit) and are measured with a kit Elisa from R&D Systems (Human IL-1 beta Quantikine(r) kit; Human TNF-alpha Quantikine(r) kit).

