## Sample size

The two primary hypotheses in this study are that Carraguard is 1) different from placebo and 2) different from no product. A primary outcome is cervico-vaginal HIV shedding measured after 7 days of daily product use. The power calculation is based on ensuring adequate power for testing these two hypotheses with this outcome with an overall significance level of 0.05. We used a 3x3 Williams design to determine power/sample size (see graph below). The Williams design is a cross-over design balanced for first carry-over effects when testing products used in sequence and will provide minimum variance unbiased estimates for the treatment effect comparisons in the presence of first order carry-over effects. It is not known whether the washout period used in this study design will be sufficient to assume no carry-over effects, hence a Williams design was employed to ensure unbiased minimum variance estimates. If there are no carry-over effects (i.e. the power will be higher than indicated) the power calculations for this design are conservative.

The null hypotheses for these primary hypotheses are: 1) No difference between Carraguard and no product and 2) no difference between Carraguard and placebo.

In order to carry out the power calculations the within subject variability needs to be specified, as well as an effect size, defined here as the average difference between a pair of treatments. Estimates of the underlying variability of genital tract HIV shedding are based on preliminary data from the CDC laboratory studies (unpublished), where the vaginal viral load was measured weekly throughout the menstrual cycle (i.e. for three weeks after menses) for 45 HIV-infected women. Based on a one-way repeated measures ANOVA, the within standard deviation of cervico-vaginal HIV shedding on the log scale was estimated as 0.66.

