## Product administration plan

Women will be instructed to insert one dose of gel, either Carraguard or placebo, vaginally every evening for the six days following the baseline visit. Women will be asked not to use other vaginal products, during the study period. Lubricated latex condoms with reservoir tips, and which are not lubricated with N-9, will be provided to limit any potential exposure to N-9. All participants will be informed that the study gel is to be used only vaginally, and that it is not designed for oral or rectal use.

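### The safeguards against Carraguard's inhibition of the RNA assay cover only the 15-minute samples: the p24 switch breaks the acute comparison, and no control is stated for the day-7 primary samples

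*Protocol*

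**What the plan says.** All references are to the Protocol.

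- **The hazard** (Methods, Specimen collection and laboratory studies): "It is known that Carraguard inhibits the RNA Amplicor test used for the cervico-vaginal supernatant specimens collected during the acute effects assessment", with the condition "if Carraguard is present in high enough quantities". No concentration limit is given.
- **The safeguards** (same section): first, "The lab protocol includes a dilution step that may be sufficient". Then, if too much Carraguard is present for RNA testing to be valid, "we will replace the RNA Amplicor test with an HIV p24 antigen test of specimens". The text does not say which arms the switch covers, or whether the pre-gel specimen is included.
- **General processing of lavage RNA** (same section): virus is pelleted by high-speed centrifugation and "a NucliSense wash will be used to extract the viral RNA prior to running the amplicor test". This is not presented as a control for Carraguard.
- **A contrast** (same section): for the gonorrhoea and chlamydia PCR, a modified procedure "will be used to eliminate all inhibition from the Amplicor test".
- **The primary time point** (Sample size): "A primary outcome is cervico-vaginal HIV shedding measured after 7 days of daily product use".
- **Dosing before that sample** (Product administration plan): gel is inserted "vaginally every evening for the six days following the baseline visit". The Study summary places day 7 one day after product use ends.
- **The acute comparison** (Objectives; Enrollment visit): a lavage and swabs are taken before gel and again about 15 minutes after, to measure the acute effect on viral load.
- **Swabs** (Appendix 7, Table 4): vaginal swabs also go to the Amplicor test, whereas the inhibition paragraph speaks only of lavage supernatant.

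**The concern.** The acute effect is a change within a woman, from before gel to 15 minutes after. RNA copies and p24 antigen are different quantities on different scales. A rule that moves the post-gel specimen to p24 and says nothing about the pre-gel one leaves that change undefined. Because the trigger is the concentration of Carraguard, a specimen-by-specimen switch would also put Carraguard samples on p24 while placebo and no-product samples stayed on RNA.

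At day 7 the question is whether enough gel remains to depress the RNA reading. On the protocol's account the inhibitor is the active gel, so neither comparator would cancel the artefact. Lower measured RNA on Carraguard alone is also what a true reduction in shedding would look like, and the same artefact could hide a true increase. The Background treats movement in either direction as a real possibility, and the risk list includes increased infectiousness. Without inhibition data, no later analysis could separate artefact from effect.

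**Working it through.** **1. The acute switch, on each reading**

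| Reading of the switch | Between arms at 15 minutes | Within woman, pre-gel to 15 minutes |
|---|---|---|
| Only specimens with too much Carraguard | Carraguard on p24, others on RNA: not comparable | p24 against RNA: not comparable |
| All 15-minute specimens, every arm | All on p24: comparable | p24 against RNA: not comparable |

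The within-woman comparison fails on both readings unless p24 is also run on the pre-gel specimen, which the text does not say.

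**2. The standard error, checked against the plan's own power statement**

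Inputs from Sample size: six sequences and three periods, carry-over in the model, 0.025 per comparison (taken as two-sided, since the hypotheses are of difference), SD 0.6 for the stated power.

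With subject, period, treatment and first-order carry-over terms, the variance of a treatment difference is (5/12)·SD² divided by the number of women per sequence, N/6. Hence SE = SD·√(2.5/N).

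- N=30, difference 0.55: SE = 0.6·√(2.5/30) = 0.173. Power is 80.5% (noncentral t, 2N−6 degrees of freedom) or 82.5% (normal).
- N=50, difference 0.43: SE = 0.6·√(2.5/50) = 0.134. Power is 82.1% (t) or 83.2% (normal).

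Both agree with the plan's claim of at least 80%, so the formula is the right one.

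**3. Illustration for day 7**

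The protocol gives no residual gel level and no size of inhibition, so the shifts below are assumptions. SD 0.66 is the estimate in Sample size, and N=50 is the larger of the two sizes used for power. Then SE = 0.66·√(2.5/50) = 0.148 and the critical value is 2.241. With no true effect and a mean under-reading b on Carraguard, the rejection probability is P(Z > 2.241 − b/SE) + P(Z < −2.241 − b/SE).

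| Mean under-reading b | b/SE | Signal loss if log10 (1 − 10^−b) | False-positive rate |
|---|---|---|---|
| 0 | 0 | 0% | 2.5% |
| 0.1 | 0.68 | 21% | 6.1% |
| 0.2 | 1.36 | 37% | 18.8% |
| 0.3 | 2.03 | 50% | 41.7% |

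The plan says only that the scale is logarithmic. The rates depend on b relative to the SD; base 10 is needed only to turn b into a percentage loss.

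The shift need not affect every sample. If a fraction f under-reads by d, the mean shift is f·d. Counting only false drops (nominal 1.25%; t distribution, SD 0.66, N=50):

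- f=10%, d=1.0 (shift 0.1): 5.8%
- f=25%, d=1.0 (shift 0.25): 28%

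**4. Masking of a rise**

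For a true rise of 0.43 (normal approximation, SE 0.148), power is P(Z > 2.241 − 0.43/0.148), about 75%. Under-reading by 0.2 leaves an apparent rise of 0.23, and power falls to about 25%.

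**The case against.** The strongest defence has four parts.

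- **The plan is not only an assay swap.** Dilution comes first and p24 is conditional on it failing. This stands.
- **A reader might infer that the Carraguard arm will be on p24 and the other arms on RNA.** The text does not say so. It can equally mean that the test is replaced for the acute time point in every arm, and staff blinded to gel identity could hardly switch by arm. This also stands as far as the arms go. It does not rescue the pre-gel pairing, which fails on either reading.
- **A reader might infer that the day-7 result is biased.** The documents do not show this. Inhibition needs a sufficient quantity of gel; the statement concerns samples taken 15 minutes after a dose, whereas day 7 is about one day after the last dose. The general pellet-and-wash processing may also reduce any residue. The defence stands against a claim of demonstrated bias, but not against the need to exclude it: the protocol does not present that processing as removing Carraguard. Women with fewer than six days of use continue gel for up to three more days before their first follow-up visit, so the interval since the last dose may vary.
- **A separate laboratory protocol exists and is not shown.** It may contain a day-7 check. One can therefore say only that this protocol states none, not that none is planned.

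**Conclusion.** The concern holds in two parts of different strength.

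The acute part is a defect in the rule as written. If p24 is used, the post-gel value loses its pre-gel reference on either reading, and on one reading the arms are split by assay as well. This needs no numerical assumption.

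The day-7 part is an unaddressed risk, not a demonstrated bias. The assay, the inhibitor and the direction of error are all in the protocol; whether any inhibition remains at day 7 is not. The rates of about 6% to 42% rest wholly on assumed mean shifts of 0.1 to 0.3 with SD 0.66 and N=50, and should not be quoted as properties of this trial. With no residual inhibition the rate is the nominal 2.5%. The figures show only that a modest shift would matter for a primary outcome, so inhibition should be excluded with data.

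**What to change.** 1. **Acute assessment.** Choose the assay once, blind to arm. If p24 is chosen, use it for the 15-minute specimens of all three arms and for the paired pre-gel specimens. On the pre-gel specimens p24 must be added to RNA, because their RNA value remains the baseline for later visits.
2. **Day 7.** Run the same arm-blind inhibition check and dilution on lavage and swab specimens from all arms. Re-run inhibited specimens at a dilution that clears inhibition, and report the number inhibited by arm. For any still inhibited, show a sensitivity analysis. Taking them as low would build the artefact into the result, and dropping them would create missing data in the Carraguard arm only.
3. **Supportive result.** Day-14 RNA is already collected, after gel has been stopped for about a week. Show it beside the primary result; no new sampling is needed.

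The cost is a few sentences in the protocol and laboratory procedure, some repeat runs, and a higher quantification limit in diluted specimens. Volume should be checked. Of a 5 mL lavage, Table 4 assigns 1 mL to RNA and 1 to 2 mL to infectious virus, which leaves at most 2 to 3 mL for p24, repeat runs and the planned cytokine tests.

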## Reimbursement, risks, and benefits

Reimbursement

Participants in this study will be given 300 Baht (approximately USD 6.50) per scheduled visit. This sum is intended to reimburse participants for transportation to and from the clinic and other potential costs associated with study participation, such as lost time from work and child care. Participants will be given 50 Baht (approximately USD 1.10) for any unscheduled visits.

Benefits

- Initial HIV medical consultation, laboratory, radiology, and pharmacy fees at Chiang Rai Hospital (Subsidized up to 1000 Baht).
- Diagnosis and treatment of reproductive tract infections
- Referral for tuberculosis preventive therapy.
- Reimbursement for the cost of 9 month tuberculosis prevention program
- One-time free laboratory testing: complete blood count and lymphocyte subset enumeration
- Participants’ partners will be treated for STIs free of charge
- Safer sex counseling
- Free condom distribution and counseling

Risks

- Vaginal lesions, including ulcerations, due to the potential toxicity of the study products
- Discomfort and/or minimal vaginal bleeding during or after pelvic examination
- Bruising and discomfort at the venipuncture site
- Psychological risks include stress on relationships if an STI is diagnosed
- Possibility of increased susceptibility to reproductive tract infections (RTIs) due to study product use
- Possibility of increased HIV infectiousness due to study product use
- Possibility of embarrassment during the pelvic examination

## Data collection and management

Case record forms are to be completed in black or blue ballpoint pen at the time of the participant visits. Information on the case record forms will be reviewed three times for completeness and clarity: by the local study staff after each study visit, at monitoring visits, and prior to data entry. The study staff will check the questionnaires and physical exam forms for completeness before the participants leave the clinic to ensure that any answers to questions missed or left blank can be ascertained. The study monitors will be responsible for assuring that the forms are properly completed and retraining of the study staff will be undertaken if necessary. Accuracy of data entry will be checked by the data analysis team who will inspect and confirm apparently aberrant responses. The laboratory scientist will complete the laboratory forms and keep duplicate records in the laboratory. Coding of adverse events and concomitant medication will be done by an experienced study team member. Case record forms will be used to create a database at the TUC. All data will be double entered and validated in Chiang Rai .

All forms will have two copies. One copy will be kept at the study site, and the original will be sent to the Population Council. To correct errors, a single line will be placed through the mistake, a date, and the initial of the person making the change will be included. No whiteout or other obscuring method will be used.

Questions emerging during the different data management steps will be sent by the Population Council data manager to the investigators. The database will be edited once the questions are resolved. Once the data has been entered and cleaned, the database will be sent to CDC.

Data analysis will be led by a CDC statistician in close collaboration with the Population Council Data Manager and the Principal Investigators from The Population Council, TUC, and CDC.

## Data analysis

Objective 1: Product safety

Primary endpoints include epithelial disruption based upon colposcopic and naked-eye exams, vaginal flora disturbances, self-reported symptoms, and acquisition of RTIs. A random effects general linear model will be used which includes parameters for subject effects, treatment effects, period effects and first-order carry-over effects.

##

Objective 2: Genital shedding of HIV

Analyses will be based on a log transformation of the genital tract HIV viral load data, as suggested by preliminary data on genital tract HIV shedding from the CDC laboratory studies (unpublished). A random effects linear model will be used to analyze the data collected at the first follow-up visit, 7 days after daily product use. This model includes parameters for subject effects, treatment effects, period effects and first-order carry-over effects (defined as carry-over effects from the previous period). The subject effect will be treated as a random effect with a normal distribution. The random error term associated with a specific period and subject within a given sequence will be assumed to have a normal distribution with a compound symmetric (uniform) covariance structure. The chosen model assumes no sequence effect, which is reasonable given subjects are being randomized to each sequence. In addition, we assume no treatment by period interaction (i.e. the effect of genital tract HIV shedding for each treatment does not depend on the period it is administered), which seems to be a reasonable assumption for this study. Wash-out periods of three weeks between each treatment are expected to lessen the chances of observing a significant carryover effect. However, since little is known about the effects of these treatments on genital tract HIV viral load, the possibility of a carry-over effect will be tested. In the absence of carry-over effects, this will be dropped from the model and we can estimate the direct effect of the treatments on genital tract HIV viral load.

Objective 3: Product acceptability

Results from the Acceptability questionnaires will be tabulated, and associations between baseline demographic and sexual behavior characteristics and indicators of acceptability will be explored.

Weekly reports on enrollment and follow-up statistics will be distributed by Chiang Rai Health Club staff to the study team to assess trends.

The definition of noncompliance is less than 6 days of study gel use reported at the first follow-up (7 day ) visit. Women who do not meet this criterion will be asked to use gel for up to 3 more days, for a maximum of 6 days. For the analysis, women who use study gel 6 of 9 days or more will be included in the per protocol analysis and those who do not meet this criterion will be included in the intention to treat analysis.

We will have a statistician review the mucosal safety data after the first 25 women have completed the first gel use arm. We will look at the differences in epithelial disruption (includes abrasions, ulcers, and fissures) from baseline to the first follow-up visit (day 7) and compare these differences between the 3 study arms. We will stop enrollment in the study and form a DMC to review the data if there is a difference between groups that is significant at the p<0.001 level, a standard stopping rule for this type of trial (Reference: Geller, N and Pocock, S. Interim Analyses in Randomized Clinical trials: Ramifications and Guidelines for Practitioners. Biometrics 43 1987 213-223).

Study participants will be provided with information regarding how to contact the Chiang Rai Health Center for study results and their blinding code when results are available. Results of the final analysis will be presented to the Chiang Rai Advisory Committee, and at local and international scientific meetings. We also plan to publish the results in the international scientific literature.

